### Sample size

The sample size was calculated using VO_2_max as the single primary outcome. VO_2_max was selected because CRF is the principal physiological endpoint of the stair-climbing ES intervention. Previous stair-climbing ES evidence has reported improvements in peak oxygen uptake (VO_2_peak) among sedentary young adults, supporting CRF as a relevant physiological endpoint for the present trial (36).

The numerical assumptions for the sample size calculation were primarily informed by a previous 12-week stair-climbing ES RCT in sedentary obese college students (42). That trial reported post-intervention VO_2_max values of 37.61 ± 3.87 and 32.06 ± 4.95 mL·kg^-^¹·min^-^¹ in the intervention and control groups, respectively (42).

Based on the pooled post-intervention SD of 4.44 mL·kg^-^¹·min^-^¹, we prespecified a target between-group of 3.5 mL·kg^-^¹·min^-^¹. This target difference was smaller than the observed between-group difference of 5.55 mL·kg^-^¹·min^-^¹ in the source trial and corresponds to approximately 1 metabolic equivalent (MET) (85). However, because the pooled SD was derived from a small RCT in sedentary obese college students, the resulting standardized effect size should be interpreted as a pragmatic planning estimate rather than a population-specific estimate for the broader sedentary university-student population. The assumed standardized effect size was Cohen’s d = 0.79.

Using G*Power version 3.1, with a two-sided alpha level of 0.05, 80% power, and a 1:1 allocation ratio, 26 participants per group were required. Allowing for 10% attrition increased the required sample size to 29 participants per group. The registered target sample size was set at 30 participants per group, yielding a total planned sample of 60 participants.

### Recruitment

This study will enlist qualified students from Shihezi University. A multi-channel recruitment strategy that uses both online and offline methods will be used. The university’s official website and WeChat public account will post online job openings. Offline job openings will be posted in public areas on campus, such as libraries, gyms, dorms, and classrooms. Everyone who wants to participate must sign up using the link or contact information given in the announcements and posters. After they sign up, they will go through the established eligibility criteria screening process.

### Assignment of interventions: allocation

#### Sequence generation

An independent researcher not involved in recruitment, baseline assessment, or intervention delivery will generate the allocation sequence using R software (version 4.4.1), with a 1:1 allocation ratio. The sequence will be generated before enrolment and retained in a password-protected file by the independent sequence custodian.

#### Concealment mechanism

Allocation will be concealed using sequentially numbered, opaque, sealed envelopes prepared by personnel independent of recruitment and assessment. Each envelope will contain the group assignment and participant identification number only. Envelopes will remain sealed until completion of baseline assessment for the corresponding participant.

#### Implementation

After baseline assessment, the next sequentially numbered envelope will be opened by an independent researcher not involved in recruitment or outcome assessment. The allocation date, participant identification number, and assigned group will be documented in an allocation log.

### Assignment of interventions: blinding

#### Who will be blinded

This trial will use blinded outcome assessment and blinded data analysis. Participants and exercise instructors cannot be blinded because the intervention involves supervised stair-climbing exercise. This limitation may introduce performance bias. To reduce detection and analytical bias, CRF test technicians, blood sample analysts, psychological evaluators, and data analysts will remain blinded to group allocation. Participants and instructors will be instructed not to disclose allocation status during assessments. Blinding-specific training will cover procedures for maintaining masking, including avoiding questions about group allocation or intervention participation, restricting access to allocation records, using assessment forms and analysis datasets without group labels, and documenting any accidental disclosure of allocation as a potential unblinding incident. Blinding will be maintained through data de-identification, procedural separation, standardized assessments, and blinding-specific training.

#### Procedure for unblinding if needed

Unblinding will be initiated only in the event of a serious adverse event requiring knowledge of allocation for participant safety. The specific procedure is as follows:

The attending physician completes a written unblinding request justifying its necessity.Upon approval by the principal investigator and the chair of the data safety monitoring board, the random sequence custodian opens the envelope to obtain allocation information.The ethics committee must be informed within 24 hours of unblinding. The participant will move to open-label management, and a backup team will do the next evaluations. The data will be marked as “unblinded” and added to the set for the intention-to-treat analysis.

### Data collection and management

#### Plans for assessment and collection of outcomes

This study will use paper case report forms as source documents during on-site assessments. Manually recorded outcome measurements will undergo point-of-assessment verification: one recorder will enter the value on the case report form, and a second recorder will verify it against the instrument display, assessor reading, or source measurement record before the participant leaves the assessment station. Immediate discrepancies will be resolved against the source measurement and documented where appropriate.

After on-site assessments, data from the paper case report forms will undergo independent double data entry into a password-protected Microsoft Excel 365 workbook. Discrepancies between the two electronic entries will be resolved against the original case report forms and documented in a correction log. Because direct electronic data capture will not be used, transcription error risk will be minimized through point-of-assessment source-value verification, independent double data entry, source-data reconciliation, and correction logging.

#### Plans to promote participant retention and complete follow-up

To promote retention and completion of scheduled procedures, standardized weekly WeChat reminders will be sent to participants. Telephone contact will be used for non-response, missed assessments, or three consecutive missed intervention sessions. All retention contacts will be documented in a retention log. Assessment sessions will be scheduled flexibly where possible. Small non-coercive completion incentives, such as certificates of participation or study-related gifts, will be provided after completion of trial assessments.

#### Data management

This study will use a three-stage data quality-control workflow:

First, point-of-assessment verification will be conducted using the dual-recorder procedure described above to reduce errors in source-data recording during on-site assessments.Second, completed case report forms will be reviewed after each assessment day for completeness, legibility, and format consistency. Missing, ambiguous, or inconsistent entries will be queried and resolved against the source documents before data entry where possible.Third, independently entered electronic datasets will be compared and reconciled against the original case report forms. A designated quality-control team will conduct weekly range, consistency, and logic checks according to prespecified validation rules. All corrections will be traceable and documented in the correction log.

Paper-based data will be stored in locked cabinets under the custody of designated personnel, whereas electronic data will be encrypted.

#### Confidentiality

Neither the paper-based nor the digital datasets will contain any individual identifiers. Participants will receive a unique research identifier to ensure data anonymity.

### Statistical methods

All statistical analyses will be conducted in R (version 4.4.1). Continuous variables will be summarised as mean ± standard deviation (SD) or median [(IQR)], as appropriate, and categorical variables as n (%). Baseline characteristics will be described descriptively for the randomised sample.

The primary analysis will follow the intention-to-treat principle. The between-group effect on post-intervention VO_2_max will be estimated using analysis of covariance (ANCOVA), with group allocation as the fixed factor and baseline VO_2_max as the covariate. The primary treatment effect will be reported as the adjusted mean difference with a 95% confidence interval (CI), and statistical inference for the primary outcome will be based on a two-sided alpha level of 0.05. If meaningful between-group imbalance in recorded compulsory PE exposure is observed, a sensitivity analysis additionally adjusted for PE exposure may be conducted to examine the robustness of the primary findings.

Secondary and exploratory outcomes will be analyzed using analogous baseline-adjusted models. Psychological outcomes will be interpreted according to the prespecified hierarchy, with BDI and PSS prioritized as key secondary psychological outcomes. Outcomes with marked skewness will be analyzed using log-ANCOVA, with exponentiated estimates reported as geometric mean ratios and percentage differences. These outcomes will be interpreted as supportive or hypothesis-generating, with emphasis on effect estimates and 95% CIs rather than confirmatory hypothesis testing. Multiplicity considerations for prespecified secondary outcome domains will be addressed in the analysis hierarchy described for those outcomes.

Missing outcome data will be handled using multiple imputation with predictive mean matching, and estimates will be pooled using Rubin’s rules. The imputation model will include group allocation, the corresponding baseline outcome value, and relevant baseline predictors. A completers-only analysis will be performed as a sensitivity analysis. All tests will be two-sided.

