### Eligibility criteria

Inclusion criteria include the following:

Full-time university students aged 18–32 years.Low self-reported physical activity, defined as ≤1.5 h/week of moderate-to-vigorous physical activity (MVPA), and high sedentary exposure, defined as ≥6 h/day of sedentary time, assessed using the International Physical Activity Questionnaire (IPAQ) (44).Completion of a health history questionnaire (45), Physical Activity Readiness Questionnaire (PAR-Q+) (46) and electrocardiogram screening to exclude potential cardiac rhythm abnormalities prior to enrollment.Provision of written informed consent and willingness to comply with the intervention and assessment procedures.

Exclusion criteria include the following:

Self-reported MVPA exceeding the eligibility threshold, or participation in additional structured exercise training outside compulsory physical education classes.Current or recent musculoskeletal, cardiovascular, respiratory, metabolic, neurological, or psychiatric conditions that may contraindicate vigorous stair-climbing exercise or limit safe participation.Use of medications or treatments that may substantially affect cardiovascular, metabolic, inflammatory, or psychological outcomes.Majoring in sports science or exercise-training-related disciplines, to minimize confounding from discipline-specific curricular training, exercise literacy, habitual structured-activity exposure, and potential intervention contamination.Inability to comply with the intervention schedule, assessment procedures, or follow-up requirements.

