##### Mental health

Psychological outcomes will be assessed using validated Chinese-language instruments selected to capture prespecified psychological and psychosocial domains relevant to sedentary university students, including depressive symptoms, perceived stress, mood state, general well-being, sleep quality, perceived social support, resilience, and body appreciation. These outcomes will be interpreted according to a prespecified hierarchical framework rather than as a single composite construct, because the selected instruments assess distinct but related psychological and psychosocial dimensions.

Depressive symptoms and perceived stress will be treated as key secondary psychological outcomes and assessed using the Beck Depression Inventory-II (BDI-II) (68) and 10-item Perceived Stress Scale (PSS-10) (69), respectively. Mood state, general well-being, and sleep quality will be treated as supportive psychological outcomes and assessed using the Profile of Mood States (POMS) (70), General Well-Being Schedule (GWBS) (71), and Pittsburgh Sleep Quality Index (PSQI) (72). Perceived social support, resilience, and body appreciation will be treated as exploratory psychosocial indicators and assessed using the Multidimensional Scale of Perceived Social Support (MSPSS) (73), Resilience Scale (74), and Body Appreciation Scale-2 (BAS-2) (75). Baseline covariates will include demographic characteristics and health behaviors, including smoking, alcohol use, and sedentary time.

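### The primary ANCOVA adjusts for baseline VO2max only; prespecifying sex as well would bring a small gain in precision at little cost

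*Protocol article*

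**What the plan says.** Under Statistical methods, the primary analysis is an intention-to-treat ANCOVA of post-intervention VO2max, "with group allocation as the fixed factor and baseline VO_2_max as the covariate". The only further adjustment is an optional sensitivity analysis for compulsory PE exposure. Secondary and exploratory outcomes use models of the same baseline-adjusted form. The imputation model contains group, the baseline value of the outcome and unspecified relevant baseline predictors.

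Under Eligibility criteria, the population is "Full-time university students aged 18–32 years", with further activity, health and course-of-study criteria but none on sex. The article never mentions sex or gender.

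Under Mental health, the article adds: "Baseline covariates will include demographic characteristics and health behaviors, including smoking, alcohol use, and sedentary time". It does not say which analysis these covariates belong to, and no model under Statistical methods names any of them.

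Under Sample size, the target is 3.5 mL/kg/min: "Based on the pooled post-intervention SD of 4.44", and "The assumed standardized effect size was Cohen’s d = 0.79". The planned total is 60.

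**The concern.** If both sexes enrol and VO2max differs between them, a single baseline measurement carries most of that difference but not all of it. The baseline is measured with error and varies within person, so its slope is below one within each sex. Some variation between the sexes then stays in the residual. The same reasoning applies to any secondary outcome that differs by sex and is analysed with the same baseline-only form.

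Two modest things are at stake. The first is the width of the primary confidence interval. The second is what happens if the arms differ noticeably in sex mix: with sex outside the prespecified model, an adjustment added afterwards would be post hoc. The promise of demographic covariates in one section and their absence from every model in another also leaves the analyst to decide later what was meant.

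**Working it through.** **The plan's own figure.** Pooled SD = √[(3.87² + 4.95²)/2] = 4.44. d = 3.5/4.44 = 0.79. By the normal approximation, n = 2(1.96 + 0.84)²/0.788² = 25.3, so 26 per group, as stated. The exact t calculation gives 27 (power 79.6% at 26 and 81.1% at 27). Then 26/0.9 = 28.9, so 29, with 30 planned. This calculation is for an unadjusted comparison, whereas the planned analysis is baseline-adjusted.

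**Assumed inputs, not in the documents.** D is the sex gap in within-sex SDs (1 to 2). r is the within-sex baseline-to-post correlation (0.5 to 0.8). The sex mix is 50:50.

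**Residual variance, in units of the within-sex variance.** Let V = 1 + D²/4 and C = r + D²/4. Without sex it is V − C²/V; with sex it is 1 − r².

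| D | r | Without sex | With sex | Reduction |
|---|---|---|---|---|
| 1 | 0.8 | 1.25 − 1.05²/1.25 = 0.368 | 0.360 | 2.2% |
| 1.5 | 0.7 | 1.5625 − 1.2625²/1.5625 = 0.542 | 0.510 | 6.0% |
| 2 | 0.5 | 2 − 1.5²/2 = 0.875 | 0.750 | 14.3% |

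**Cost of the term.** Going from one to two covariates multiplies the expected variance of the treatment effect by about (N − 4)/(N − 5). That is 50/49 = 1.020 at N = 54 and 56/55 = 1.018 at N = 60, so about 2%.

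**Net interval width, at N = 54.**
- D = 1, r = 0.8: √(0.978 × 1.020) = 0.999, about unchanged.
- D = 1.5, r = 0.7: √(0.940 × 1.020) = 0.979, about 2% narrower.
- D = 2, r = 0.5: √(0.857 × 1.020) = 0.935, about 6.5% narrower (7.4% before the cost).

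**Power.** This takes 27 completers per group, a difference of 3.5, a within-sex SD of 4.44 and a 50:50 mix. The degree of freedom is charged, but the imbalance part of the 2% is not.

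| Sex gap (mL/kg/min) | r | Baseline only | Baseline + sex | 95% CI half-width |
|---|---|---|---|---|
| 6 | 0.5 | 87.7% | 90.7% | 2.21 vs 2.10 |
| 6 | 0.7 | 97.2% | 97.8% | 1.78 vs 1.73 |
| 6 | 0.8 | 99.6% | 99.7% | 1.48 vs 1.46 |
| 10 | 0.5 | 85.4% | 90.7% | 2.29 vs 2.10 |
| 10 | 0.7 | 96.7% | 97.8% | 1.82 vs 1.73 |

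A gap of 6 is 6/4.44 = 1.35 SDs. A gap of 10 is 2.25 SDs, slightly beyond the range above.

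**Chance imbalance.** Suppose 30 of 60 participants are women, the arms are 30:30 and allocation is not balanced on sex. The hypergeometric probability that the sex shares differ by 20 points or more is 0.196. Given a 20-point difference, the shift left in the baseline-adjusted estimate is 0.20 × D × (1 − C/V).
- D = 1, r = 0.8: 0.20 × 1 × 0.16 = 0.032 SD, or 0.14 mL/kg/min at SD 4.44.
- D = 2, r = 0.5: 0.20 × 2 × 0.25 = 0.10 SD, or 0.44 mL/kg/min.

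Both are small against the target of 3.5.

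**The case against.** The strongest reply is that nothing here is wrong. ANCOVA on the baseline value of the outcome is the natural choice, it is unbiased under randomisation whether or not sex is included, and a single covariate is defensible in a trial of 60. Baseline VO2max already absorbs most of any sex difference. The gain depends on inputs that the article does not give, and even a mixed-sex sample is inferred from the absence of a restriction. All of that stands. It limits the point to an optional improvement in a model that the article does state in full.

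A reader might infer three stronger things, and the documents support none of them.

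- **That allocation is simple randomisation.** The article says only that an independent researcher "will generate the allocation sequence using R software (version 4.4.1), with a 1:1 allocation ratio". Silence on blocks and strata does not mean there are none: an article commonly leaves these to the full protocol, and a target of 30 per group is compatible with a restricted sequence. Even a 34:26 split would raise the standard error by only 0.9%, since √[(1/34 + 1/26)/(2/30)] = 1.009.
- **That the stated 80% power has little slack.** The figure belongs to an unadjusted comparison. At SD 4.44 and 27 per group, with no sex gap, baseline adjustment alone gives 90.7% at a correlation of 0.5 and 97.8% at 0.7, against 81.1% unadjusted. The Discussion already discloses that greater VO2max variability may lower power.
- **That the change is free.** It costs a degree of freedom and about 2% in variance. If there were no sex gap, that cost would be a small net loss.

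**Conclusion.** The point holds as a minor efficiency suggestion with one textual gap attached. The primary model omits sex although sex is not restricted, and the demographic covariates promised under Mental health are not placed in any model. Under assumed sex gaps of 1 to 2 within-sex SDs and within-sex correlations of 0.5 to 0.8, adding sex removes 2% to 14% of residual variance before a cost of about 2%. Net, the interval is between about unchanged and 7% narrower, and power rises by about 0 to 5 points, mostly by 1 point or less once the correlation reaches 0.7. The validity of the primary test is not in question, and its power stays above 85% in every scenario computed. The size of the gain rests entirely on the assumed gap, correlation and sex mix.

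**What to change.** Prespecify sex as a covariate in the primary ANCOVA and in the analogous secondary and exploratory models, including those on the log scale. Name it explicitly in the imputation model, so that imputation and analysis agree. Reconcile the Mental health statement with Statistical methods by listing which demographic and behavioural covariates enter which model, or by saying that they are descriptive only.

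The cost is one degree of freedom, about 2% in expected variance, and an amendment through the ethics committee as the article requires. The gain is small or nil if the baseline-to-post correlation turns out high. The change can still be made after recruitment starts, provided it is fixed before anyone sees outcome data by group.

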### Oversight and monitoring

#### Composition of the coordinating center and trial steering committee

The central coordination unit will include data collection staff and research personnel tasked with recruiting participants, collecting data, and implementing interventions. The trial oversight committee will consist of the lead investigator and collaborating investigators, with responsibilities including finalizing the intervention protocol, personnel training, and overall trial supervision.

#### Composition of the data monitoring committee, its role and reporting structure

Given the low-risk nature, short duration, and modest sample size of this trial, a formal independent Data Monitoring Committee was not considered necessary. Safety oversight will be undertaken by the principal investigator and the trial steering team, who will review participant safety, protocol adherence, and any adverse events throughout the study. Any serious adverse event will be managed according to the prespecified emergency response procedures and reported to the ethics committee as required.

#### Adverse event reporting and harms

To prevent and address potential acute health risks during the intervention, an emergency response protocol and adverse event recording form have been established in addition to insurance coverage. This protocol seeks to guarantee participant safety and uphold study compliance by implementing standardized procedures for the collection, evaluation, management, and reporting of adverse events. **Figure 4** shows that information is gathered through on-site observation and participant reports, and then it is sorted by severity. Severe events require immediate first aid and activation of Emergency Medical Services (EMS), while non-severe events are managed on-site. All events must be documented using the recording form, with severe events reported to the ethics committee within a specified timeframe and non-severe events summarized periodically.

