## Methods and analysis

### Study design

This study is the first experiment within a prospectively planned, multiphase randomized controlled trial program and is designed as a two-arm, parallel-group, superiority trial with 1:1 allocation, blinded outcome assessment, and blinded data analysis. The trial is registered under an overarching Chinese Clinical Trial Registry record (ChiCTR2500106549), which includes six prespecified experiments conducted under a single registration number and a shared prespecified outcome framework. Within this registered program, the recruitment dates reported in the registry refer to the recruitment period for the present experiment described in this protocol. The present experiment is designed to evaluate the effects of a 12-week ES intervention on physical and mental health outcomes in sedentary university students. Subsequent experiments within the registered program will be recruited separately in accordance with their respective protocols and prespecified eligibility procedures. Participants allocated to the ES group will undertake a 12-week progressive stair-climbing intervention. During the trial period, control participants will maintain their usual lifestyle and complete the same scheduled assessments. The protocol was developed in accordance with the SPIRIT 2025 statement (**Figure 1**; Additional file 1) (43), and the participant flow diagram is presented in **Figure 2**.

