### Interventions

#### Explanation for the choice of comparators

A usual-lifestyle control group will be used as a non-exercise comparator to estimate the effects of the structured stair-climbing ES intervention. The same dietary-recording procedure will be applied to both groups. Self-reported Physical activity and sedentary time will be assessed using the IPAQ at baseline and post-intervention, with no continuous device-based monitoring of free-living physical activity or sedentary behavior planned during the 12-week trial. Trial-related contact with control participants will be limited to assessment scheduling, safety reporting, and completion of required study records.

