**Figure 3 f3:**
[figure not shown]
Overview of group allocation, intervention delivery, and outcome assessment. Participants are allocated to the exercise-snacks group or control group. The diagram summarizes the stair-climbing exercise-snack regimen, including warm-up, stair-climbing bouts, active recovery, progression from 3 to 4 bouts, between-session intervals, and common assessment procedures. CRF, cardiorespiratory fitness; HRmax, age-predicted maximal heart rate.

**Table 1 T1:** FITT-based prescription of the stair-climbing exercise-snack intervention.

Phase	Weeks 1–6	Weeks 7–12
Frequency	3 days/week; 3 sessions/day; 3 bouts × 30 s/session	3 days/week; 3 sessions/day; 4 bouts × 30 s/session
Intensity	80%–95% HRmax	80%–95% HRmax
Time	90 s/session; 270 s/day; 810 s/week	120 s/session; 360 s/day; 1080 s/week
Type	Stair climbing	Stair climbing
Volume	54 sessions; 162 bouts; 4860 s	54 sessions; 216 bouts; 6480 s
Progression	Initial adaptation phase with 3 bouts/session	Progression phase with 4 bouts/session after Week 6

FITT, frequency, intensity, time, and type; HRmax, maximal heart rate; s, seconds. Exercise time refers to accumulated stair-climbing sprint time and excludes active recovery. Exercise time and phase volume refer to accumulated stair-climbing sprint time and exclude active recovery. The control group maintained usual lifestyle and received no prescribed ES intervention during Weeks 1–12.

**Table 2 T2:** Prior exercise-snack and related short-bout exercise studies considered during intervention development.

Study	Context and mode	Key protocol features	Duration/window	Role in present protocol
Francois et al. (34)	Individuals with insulin resistance; incline treadmill walking	Exercise snacking consisted of 6 × 1-min work bouts at approximately 90% HRmax, with 1-min slow-walking recovery between bouts, completed 30 min before meals	Acute crossover exercise-trial design	Provided contextual evidence for time-distributed planned exercise snacks; not used as the primary source for the final stair-climbing FITT structure
Allison et al. (35)	Previously untrained women; brief intense stair climbing	Brief intense stair-climbing protocols included repeated 20-s or 60-s stair-climbing efforts performed as vigorous or all-out exercise	6-week training protocols	Provided contextual evidence that brief intense stair-climbing protocols can improve cardiorespiratory fitness

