The Firstbeat Bodyguard 2 device (Firstbeat Technologies Ltd., Jyväskylä, Finland) will be used as the primary heart-rate recording device, and the HUAWEI WATCH 4 Pro (Huawei Technologies Co., Ltd., Shenzhen, China) will be used for real-time heart-rate feedback during supervised sessions.During warm-up and recovery periods, participants will be instructed to maintain a light-to-moderate intensity corresponding approximately to 50%–70% of predicted HRmax. During each stair-climbing set, the target intensity will be 80%–95% of predicted HRmax (49).Before each session, participants will complete a standardized 30-s dynamic warm-up consisting of 10 s of jumping jacks, 10 s of high knees, and 10 s of tuck jumps.All sessions will be supervised by qualified exercise instructors. Immediately after each session, subjective exertion will be recorded using the Borg 6–20 Rating of Perceived Exertion (RPE) scale (50).

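### As described, adverse events are looked for far more often in the exercise-snack arm than in controls, so any by-arm summary of harms would partly reflect how closely each arm was watched

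*Protocol article*

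**What the plan says.** All references are to the protocol article.

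- **How events are found.** Under Adverse event reporting and harms, "information is gathered through on-site observation and participant reports, and then it is sorted by severity". The same section gives the purpose of the procedure: "To prevent and address potential acute health risks during the intervention, an emergency response protocol and adverse event recording form have been established". Every event is to be documented, and non-severe ones are to be summarized from time to time.
- **Observation in the ES arm.** Intervention description: "All sessions will be supervised by qualified exercise instructors". Table 1 gives "54 sessions; 162 bouts; 4860 s" for weeks 1–6 and "54 sessions; 216 bouts; 6480 s" for weeks 7–12.
- **Contact with controls.** Explanation for the choice of comparators: "Trial-related contact with control participants will be limited to assessment scheduling, safety reporting, and completion of required study records". Study design adds that "control participants will maintain their usual lifestyle and complete the same scheduled assessments". Participant timeline names two main assessment points, baseline and post-intervention.
- **Other contacts.** Plans to promote participant retention and complete follow-up says that "standardized weekly WeChat reminders will be sent to participants", with no restriction to one arm and no mention of a question about symptoms. Provisions for post-trial care adds one health call three months after the trial.
- **Status of harms.** They are not listed among the primary, secondary or exploratory outcomes, and Statistical methods contains no adverse event comparison.

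**The concern.** Harms can be compared fairly between randomized arms only if they are looked for in the same way and about equally often in each. Here one of the two stated routes is tied largely to attendance at the stairwell, which controls do not share.

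Two things follow:

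- Minor events that students have with or without the intervention, such as muscle or joint pain, dizziness or a respiratory illness, are more likely to be noticed and written down in the ES arm.
- ES events that appear after the participant has gone, such as delayed knee or calf pain, fall outside observation and rest on the participant choosing to report them.

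The first would make the intervention look worse than it is, and the second would make it look better. Neither could be separated from true harm afterwards. At stake is how any adverse event summary can be read, not the efficacy result.

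**Working it through.** **1. Session count.** From Table 1: 3 days/week × 3 sessions/day × 6 weeks = 54 per phase, and 54 + 54 = 108. This reproduces the plan's own figures and assumes full attendance.

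**2. Planned on-site occasions after randomization.** Envelopes stay sealed until baseline assessment is complete (Concealment mechanism), so baseline does not count.

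| Arm | Supervised sessions | Post-intervention assessment | Total |
|---|---|---|---|
| ES | 108 | 1 | 109 |
| Control | 0 | 1 | 1 |

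The post-intervention assessment is counted as one occasion, although it may spread over up to a week.

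**3. Do other contacts close the gap?**

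- Safety reporting is one of the permitted contacts with controls. The text gives no schedule and does not say whether it is prompted.
- The weekly WeChat messages are described as reminders, not as a harms query.
- The three-month call comes after the trial, so at best it recovers events of weeks 1–12 from memory.

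None of these, as described, is a common scheduled query during the intervention.

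**4. Possible size.** The article gives no adverse event rates, so every rate here is an assumption. Let *p* be the true risk, equal in both arms, and let *c* be the share of affected participants whose event is recorded.

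Expected number recorded per arm = 30 × *p* × *c*

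Apparent risk ratio = (*p* × *c*_ES) / (*p* × *c*_control) = *c*_ES / *c*_control

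The true ratio is 1 and *p* cancels. With *p* = 20% and *c*_ES = 90%, the ES arm records 30 × 0.20 × 0.90 = 5.4.

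| Control capture | Recorded in control | Apparent ratio |
|---|---|---|
| 90% | 5.4 | 1.0 |
| 60% | 30 × 0.20 × 0.60 = 3.6 | 0.90/0.60 = 1.5 |
| 45% | 30 × 0.20 × 0.45 = 2.7 | 0.90/0.45 = 2.0 |
| 30% | 30 × 0.20 × 0.30 = 1.8 | 0.90/0.30 = 3.0 |

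**5. Sensitivity to the ES capture rate.** If delayed ES events are often missed, 90% is too high. With *c*_ES = 60%, the same three control rates give 0.60/0.60 = 1.0, 0.60/0.45 = 1.33 and 0.60/0.30 = 2.0. The inflation shrinks and can vanish, but under-recording in the ES arm takes its place.

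**The case against.** The strongest case on the other side has five parts.

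- **Observation is not confined to ES.** A reader might infer that on-site observation exists only in that arm. It does not: controls attend the same assessments, including the maximal treadmill test. Only observation at sessions is exclusive to ES. This stands, and the count above includes the shared visit.
- **Controls have a reporting route.** A reader might infer that they can report only on their own initiative. The article names safety reporting among the permitted contacts and does not say whether it is solicited. This stands as far as it goes, but an undescribed route cannot be assumed to match 108 supervised sessions.
- **No safety comparison is planned.** It would be too strong to say that the trial fails to support its safety comparison, because none is stated. Likewise, the low risk of injury under Provisions for post-trial care is a premise drawn from earlier studies, not a claim this trial sets out to prove. Both parts stand. The point bears only on harms reported by arm, which readers of a two-arm trial are likely to do with event summaries.
- **The article is condensed.** The recording form and the flowchart in Figure 4 are not shown and may contain a common query. This stands as a limit on certainty: unequal ascertainment is likely as described, not established. The point does not rest on silence alone, because the article does state its method, and that method reaches the arms unequally.
- **The capture rates are invented.** True. They show direction and possible size only, and the lower ES rate shows that the net effect could be small.

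**Conclusion.** The point holds in a limited form. As described, harms ascertainment differs by arm: 109 planned on-site occasions after randomization in ES against 1 in controls, with no common scheduled query. Any by-arm summary of adverse events is therefore likely to mix true harm with intensity of observation, mainly for minor events, and delayed ES events depend on unprompted reports.

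The size of the bias is unknown. Apparent risk ratios of 1.5 to 3.0 with no true difference follow from an assumed 90% capture in ES and 60% to 30% in controls. A lower ES capture pulls them towards 1. The conclusion assumes that the unseen recording form adds no query put equally to both arms.

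The primary VO2max analysis is not affected. This is an inexpensive improvement to harms reporting, not a defect in the main inference.

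**What to change.** 1. Add one fixed harms question to the weekly WeChat message, worded identically for both arms, through week 12. For example: *Since last week, have you had any injury, pain, illness or other symptom? If yes, please describe.*
2. Confirm in the text that controls receive this message. The retention section says participants without naming arms, while Strategies to improve adherence to interventions describes weekly reminders as support for attending sessions.
3. Ask the same question of everyone at the post-intervention visit.
4. Base any by-arm summary of adverse events on these solicited answers. List instructor-observed events separately as ES-arm events.
5. If this is not done, state that adverse event counts will not be compared between arms.

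The existing handling and reporting of severe events stays as it is.

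The cost is one line in a message, one item at the visit and one column in the adverse event log. The downside is a few more minor events recorded and a small weekly burden on participants.
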